## Appendix F – Variceal Management Assessment

**Timepoint ASSESSMENT COMPLETED:**  Baseline - Date: ____ / ____/ _____

End of Trial - Date: ____ / ____/ _____

| ***VARICES*** | | **Yes** | **No** |
| --- | --- | --- | --- |
| 1 | Has the patient had an Endoscopy? (if no, add to care plan to refer for screening) |  |  |
| 2 | Has the patient ever had a variceal bleed? (If yes, add to care plan) |  |  |
| 3 | Confirm education given regarding variceal bleeding cause and prevention |  |  |
| 4 | Assessment of eligibility for Baveno VI Criteria  Fibroscan < 25kPa – Date fibroscan done __ / __ / ____  Platelets > 110 – Platelet level ______ Date __ / __ / ____  If fibroscan not done, ensure this is on the care plan |  |  |
| 5 | What was the date and outcome of the most recent endoscopy?  Date: ____ / ____/ _____  No varices  Small varices (<5mm, or Grade 1 or 2)  Large varices/High risk varices (>5mm, or Grade 3)  No endoscopy done  Endoscopy not required due to Baveno VI criteria |  |  |
| 6 | According to the outcome above and the protocol for variceal screening and surveillance, what is the plan of care? (ensure add to care plan and recalls)  Baveno VI criteria – fibroscan due ____ / ____ /_______  Endoscopy in 3 years due ____ / ____ /_______  Endoscopy in 2 years due ____ / ____ /_______  Endoscopy in 1 year due ____ / ____ /_______  Variceal Ligation (eradication) ____ / ____ /_______  TIPS done ____ / ____ /_______  Primary prophylaxis (please add to medication chart and care plan)  Secondary prophylaxis post variceal bleed (please add to medication chart and care plan) |  |  |
| 7 | Was the patient adherent to variceal bleeding prevention protocols (answer only at end of trial) |  |  |
| 8 | Prophylaxis – primary or secondary  What is the patient’s pulse rate? ____________ bpm  (ensure that the patient is resting comfortably for 10 minutes prior to taking pulse rate) |  |  |

Comments:

## Appendix G – Nutrition Assessment

**Timepoint ASSESSMENT COMPLETED:**  Baseline - Date: ____ / ____/ _____

End of Trial - Date: ____ / ____/ _____

| ***Nutrition*** | | **Yes** | **No** |
| --- | --- | --- | --- |
| 1 | Has patient seen a dietitian about their liver disease? |  |  |
| 2 | Does patient have:  Obvious malnutrition  Concomitant diabetes  Refractory ascites  Struggling/not understanding diet or restrictions  Then dietitian referral is required. Date referred: ___ / ___ / _____ |  |  |
| 3 | Has the nutrition action plan been discussed with the patient? |  |  |

## Appendix H – Carer and GP Assessment

Post randomisation (intervention only) - Date: ___ / ___/ __

| ***CARER*** | | **Yes** | **No** |
| --- | --- | --- | --- |
| 1 | Does the patient have a carer? |  |  |
| 2 | If yes, does the carer have any concerns/issues regarding the patient’s liver disease? |  |  |
| 3 | Ensure that if carer living with the patient that the carer is educated using the liver disease booklet. |  |  |
| 4 | Does Carer need more support or information about accessing support?  If Yes – describe: |  |  |

Comments: _______________________________________________________________

| ***General Practitioner*** | | **Yes** | **No** |
| --- | --- | --- | --- |
| 1 | Does the patient have a regular GP? If no, enter this on the care plan and ensure patient gets access to regular GP/regular GP Practice. |  |  |
| 2 | Are GP Details documented? If No, ensure details documented |  |  |
| 3 | Indicate which of the following the patient needs:  GP Management Plan (good for most patients)  Team Care Arrangement (best for patients with multiple chronic diseases)  Mental Health Care Plan - (best for patients with alcohol dependence/abuse issues) patient will get money back from [Medicare](https://www.healthdirect.gov.au/medicare) for up to 10 individual or 10 group appointments with an [allied mental health service](https://www.healthdirect.gov.au/allied-health) in a year.  If any of these required, enter onto care plan and provide information required to GP |  |  |
| 4 | Call patient’s general practitioner informing them of patients involvement in chronic liver disease case management.  Record how the GP would like their updates about their patient:  Fax (record fax number) ______________________  Email (record email address) __________________________  Telephone (ensure right telephone number) ________________________ |  |  |

Comments:

## Appendix I – Home visit form

| Date | Date of Home Visit ____ /_____ /_____  DD / MMM / YYYY |
| --- | --- |
| Timing | Scheduled within 7 days of hospitalization  Rapid response for review of symptoms  Time at start _____ Time at end _______ total number of minutes ___________ |
| Rapid response? | If Rapid response, what is the symptom for review:  _________________________________________________________________  N/A - scheduled |
| Education Booklet | Confirm that patient still has education booklet (if not provide another one)  Continue education – particularly regarding symptoms the patient may not have experienced yet |
| S&S | Assess for other signs of complications for liver disease not previously diagnosed or may have been diagnosed since seeing the patient last.  Consider assessment for mild HE – NCT and Encephalapp |
| Medication Management | Discuss medication management – look at the patient’s answers to the ask12 medication survey and come up with strategies.  Would a webster pack assist adherence? Y  N  (if Yes, add to care plan and arrange)  Ensure that medications prescribed are available to patient  Check the medicine cupboard and around the home. Are there out of date medications? Are they doubling up on some medications, not taking medications, confused about what to take when? Do they need a home medicines review from a pharmacist? |
| Carer support | Consider the needs of a person’s carer. Can they continue to provide care and support? Is there a backup person/plan if the main carer becomes ill or needs some respite/holidays?  Ensure the carer knows about the booklet and encourage them to read it.  Carer is aware of liver nurse phone number and when to call |
| Care Plan | Please see overleaf some other issues you may wish to consider  Ensure all new issues and interventions are added to Care Plan  Ensure patient aware of specialist appointment date |

Study Coordinator (print) : ___________________ Signature: ________________________ Other home visit considerations:

- Assess self-management, anxiety, depression and lifestyle risks
- What are the health problems of greatest importance to the patient?
- What about their tobacco and alcohol use, sleep patterns, physical activity and nutrition?
- Consider psychosocial factors such as their perception of loneliness, bereavement or loss of motivation.
- What are their social needs and the extent and availability of social support? (including family, carers, neighbours and friends)
- Ask questions about hobbies, pets and activities to understand if the patient is socially isolated?
- Consider mobility and balance, including walking, transfers and climbing stairs. Are they currently in pain? Consider use of a pain score.
- maintaining personal hygiene, including bathing, grooming, toileting, continence and dressing
- eating and drinking. Are daily activities (chores, meal preparation, shopping) a problem?
- What transport do they use? Do they shop, prepare meals? How do they manage with home maintenance and housekeeping?
- Consider the abilities and limitations within the person’s living environment including safety issues, which may require resolution (ie slip/trip hazards, equipment, personal alarm)
- Is transport assistance required? Does the patient need assistance with making and attending appointments with specialists/allied health, etc

## Appendix J – Hospital Admission Log

Date of randomisation: ___ / ___ / ____

**Period of review (tick only one):**

□ Randomisation Date ___ / ___ / ____ to 12 months ___ / ___ / ____

□ 12 months ___ / ___ / ____to trial end ___ / ___ / ____

( NB If currently in hospital this counts as an admission in the time period being considered)

| Admission 1 |
| --- |
| Admission Date ___ / ___ / ____ Medically Stable for D/C Date ___ / ___ / ____  Discharge Date ___ / ___ / ____  Primary reason for admission as per D/C summary: __________________________  Liver Related Yes  No  Was this a decompensation Event? Yes  No  Emergency  or Elective  (Tick only one)  Number of days in ICCU (please state ‘0’ if not in ICCU): _______ |
| Admission 2 |
| Admission Date ___ / ___ / ____ Medically Stable for D/C Date ___ / ___ / ____  Discharge Date ___ / ___ / ____  Primary reason for admission as per D/C summary: __________________________  Liver Related Yes  No  Was this a decompensation Event? Yes  No  Emergency  or Elective  (Tick only one)  Number of days in ICCU (please state ‘0’ if not in ICCU): _______ |
| Admission 3 |
| Admission Date ___ / ___ / ____ Medically Stable for D/C Date ___ / ___ / ____  Discharge Date ___ / ___ / ____  Primary reason for admission as per D/C summary: __________________________  Liver Related Yes  No  Was this a decompensation Event? Yes  No  Emergency  or Elective  (Tick only one)  Number of days in ICCU (please state ‘0’ if not in ICCU): _______ |
| Admission 4 |
| Admission Date ___ / ___ / ____ Medically Stable for D/C Date ___ / ___ / ____  Discharge Date ___ / ___ / ____  Primary reason for admission as per D/C summary: __________________________  Liver Related Yes  No  Was this a decompensation Event? Yes  No  Emergency  or Elective  (Tick only one)  Number of days in ICCU (please state ‘0’ if not in ICCU): _______ |

| Admission 5 |
| --- |
| Admission Date ___ / ___ / ____ Medically Stable for D/C Date ___ / ___ / ____  Discharge Date ___ / ___ / ____  Primary reason for admission as per D/C summary: __________________________  Liver Related Yes  No  Was this a decompensation Event? Yes  No  Emergency  or Elective  (Tick only one)  Number of days in ICCU (please state ‘0’ if not in ICCU): _______ |
| Admission 6 |
| Admission Date ___ / ___ / ____ Medically Stable for D/C Date ___ / ___ / ____  Discharge Date ___ / ___ / ____  Primary reason for admission as per D/C summary: __________________________  Liver Related Yes  No  Was this a decompensation Event? Yes  No  Emergency  or Elective  (Tick only one)  Number of days in ICCU (please state ‘0’ if not in ICCU): _______ |
| Admission 7 |
| Admission Date ___ / ___ / ____ Medically Stable for D/C Date ___ / ___ / ____  Discharge Date ___ / ___ / ____  Primary reason for admission as per D/C summary: __________________________  Liver Related Yes  No  Was this a decompensation Event? Yes  No  Emergency  or Elective  (Tick only one)  Number of days in ICCU (please state ‘0’ if not in ICCU): _______ |
| Admission 8 |
| Admission Date ___ / ___ / ____ Medically Stable for D/C Date ___ / ___ / ____  Discharge Date ___ / ___ / ____  Primary reason for admission as per D/C summary: __________________________  Liver Related Yes  No  Was this a decompensation Event? Yes  No  Emergency  or Elective  (Tick only one)  Number of days in ICCU (please state ‘0’ if not in ICCU): _______ |
| Admission 9 |
| Admission Date ___ / ___ / ____ Medically Stable for D/C Date ___ / ___ / ____  Discharge Date ___ / ___ / ____  Primary reason for admission as per D/C summary: __________________________  Liver Related Yes  No  Was this a decompensation Event? Yes  No  Emergency  or Elective  (Tick only one)  Number of days in ICCU (please state ‘0’ if not in ICCU): _______ |

## Appendix K – Outpatient Attendance Log

Date of randomisation: ___ / ___ / ____

Period of review (tick only one):

Randomisation Date ___ / ___ / ____ to 12 months ___ / ___ / ____

12 months ___ / ___ / ____to trial end ___ / ___ / ____

| Outpatient review 1 |
| --- |
| Appointment Date ___ / ___ / ____  Attended? Yes  No  If no Why? Did not turn up  Cancelled |
| Outpatient review 2 |
| Appointment Date ___ / ___ / ____  Attended? Yes  No  If no Why? Did not turn up  Cancelled |
| Outpatient review 3 |
| Appointment Date ___ / ___ / ____  Attended? Yes  No  If no Why? Did not turn up  Cancelled |
| Outpatient review 4 |
| Appointment Date ___ / ___ / ____  Attended? Yes  No  If no Why? Did not turn up  Cancelled |
| Outpatient review 5 |
| Appointment Date ___ / ___ / ____  Attended? Yes  No  If no Why? Did not turn up  Cancelled |
| Outpatient review 6 |
| Appointment Date ___ / ___ / ____  Attended? Yes  No  If no Why? Did not turn up  Cancelled |

| Outpatient review 7 |
| --- |
| Appointment Date ___ / ___ / ____  Attended? Yes  No  If no Why? Did not turn up  Cancelled |
| Outpatient review 8 |
| Appointment Date ___ / ___ / ____  Attended? Yes  No  If no Why? Did not turn up  Cancelled |
| Outpatient review 9 |
| Appointment Date ___ / ___ / ____  Attended? Yes  No  If no Why? Did not turn up  Cancelled |
| Outpatient review 10 |
| Appointment Date ___ / ___ / ____  Attended? Yes  No  If no Why? Did not turn up  Cancelled |
| Outpatient review 11 |
| Appointment Date ___ / ___ / ____  Attended? Yes  No  If no Why? Did not turn up  Cancelled |
| Outpatient review 12 |
| Appointment Date ___ / ___ / ____  Attended? Yes  No  If no Why? Did not turn up  Cancelled |
| Outpatient review 13 |
| Appointment Date ___ / ___ / ____  Attended? Yes  No  If no Why? Did not turn up  Cancelled |

If more than 13 appointments in 12 months, please print this page a second time.

## Appendix L – West Haven Criteria

**Date of assessment ____ / ____ / ________**

| **West Haven Criteria** | |
| --- | --- |
| Grade | Criteria |
| 1 | Trivial lack of awareness |
|  | Euphoria or anxiety |
|  | Shortened attention |
|  | Impaired performance of addition |
| 2 | Lethargy or apathy |
|  | Minimal disorientation of time or place |
|  | Subtle personality changes |
|  | Inappropriate behaviour |
|  | Lethargy or apathy |
| 3 | Somnolence to semi-stupor but responsibe to verbal stimuli |
|  | Confusion |
|  | Gross disorientation |
| 4 | Coma (unresponsive to verbal or noxious stimuli) |

Principal Investigator : ______________________________

Signature: ______________________________________

Date: _________________________

## Appendix M – Contact Log

| **Nurse Contact Log** | **ALFIE** | Participant  ID | Participant Initials |
| --- | --- | --- | --- |
|  |  | __- __ __ __ | __ __ __ |

This is completed for all Intervention patients to document all contacts with the patient or their GP.

| **Contact type** | **Date** | **SIGNED** |
| --- | --- | --- |
| Scheduled Home Visit  Unscheduled Home visit (rapid response)  Scheduled telephone contact  Unscheduled telephone contact  GP Fax/ Email / Telephone call (please circle which one) | ____/______/___  DD/MMM/YY | ____________ |
| Scheduled Home Visit  Unscheduled Home visit (rapid response)  Scheduled telephone contact  Unscheduled telephone contact  GP Fax/ Email / Telephone call (please circle which one) | ____/______/___  DD/MMM/YY | ____________ |
| Scheduled Home Visit  Unscheduled Home visit (rapid response)  Scheduled telephone contact  Unscheduled telephone contact  GP Fax/ Email / Telephone call (please circle which one) | ____/______/___  DD/MMM/YY | ____________ |
| Scheduled Home Visit  Unscheduled Home visit (rapid response)  Scheduled telephone contact  Unscheduled telephone contact  GP Fax/ Email / Telephone call (please circle which one) | ____/______/___  DD/MMM/YY | ____________ |
| Scheduled Home Visit  Unscheduled Home visit (rapid response)  Scheduled telephone contact  Unscheduled telephone contact  GP Fax/ Email / Telephone call (please circle which one) | ____/______/___  DD/MMM/YY | ____________ |
| Scheduled Home Visit  Unscheduled Home visit (rapid response)  Scheduled telephone contact  Unscheduled telephone contact  GP Fax/ Email / Telephone call (please circle which one) | ____/______/___  DD/MMM/YY | ____________ |
| Scheduled Home Visit  Unscheduled Home visit (rapid response)  Scheduled telephone contact  Unscheduled telephone contact  GP Fax/ Email / Telephone call (please circle which one) | ____/______/___  DD/MMM/YY | ____________ |

Print more as required.

## Appendix N– Child Pugh and MELD Score

**Timepoint ASSESSMENT COMPLETED:**  Baseline - Date: ____ / ____/ _____

3 month - Date: ____ / ____/ _____

6 month - Date: ____ / ____/ _____

Intervention only

12 month - Date: ____ / ____/ _____

18 month - Date: ____ / ____/ _____

End of Trial - Date: ____ / ____/ _____

| CHILDS PUGH SCORE – go to [**https://www.mdcalc.com/child-pugh-score-cirrhosis-mortality**](https://www.mdcalc.com/child-pugh-score-cirrhosis-mortality) | |
| --- | --- |
| Blood test date: ____________________ (most recent – closest to date due)  Bilirubin: ______  Albumin: ______  INR: __________  **Ascites**  None  Slight/controlled on treatment  Moderate | **HE**  None  Grade 1-2  Grade 3-4  **RESULT**  A5  A6  B7  B8  B9  C10  C11  C12 |
| MELD- go to [**https://www.mdcalc.com/meld-score-model-end-stage-liver-disease-12-older**](https://www.mdcalc.com/meld-score-model-end-stage-liver-disease-12-older) | |
| Dialysis ≥ 2 times in the past week?  No  Yes  From Blood test date: ______________________  Creatinine: ___________  MELD _______________  Bilirubin: _____________  INR: ________________  Na+: ________________ | |

Comments:

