## Outpatient review by Specialist Gastroenterologist/Hepatologist

Review by a specialist must be scheduled within 1 month (4 weeks) of discharge from hospital for all patients in the intervention group. The nurse must attend this appointment with the patient. In preparation for the outpatient appointment the following should be updated:

- - Medication list
  - Care Plan
  - Ensure screening and surveillance requirements are up to date (or booked)

At this appointment the specialist will discuss the care plan with the nurse and the patient and sign off on the care plan.

## Month 3, Month 6, Month 12, Month 18

Patients in the intervention group have their Child Pugh and Meld scores completed at 3, 6, 12, 18 months and at end of trial (Appendix N). Collect the information from the most recent bloods taken as part of usual care, the patient will not be required to have a blood test taken just for this score to be done.

Surveys are due for both groups at this time. For intervention patients this should ideally be scheduled at the same time the specialist outpatient appointment is scheduled to enable accurate determination of the Child Pugh and MELD score. Ensure the contact log is up to date. Patients will be provided the option of receiving the surveys via standard post or electronically, via email, at consent.

Record hospital and liver-related outpatient admissions/attendances/non attendances at the month 12 visit.

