## Mortality and disease severity

Mortality at end of study follow up will be a further secondary endpoint of the study. To ensure patients lost to follow up have not died, cross checking with Australian death registries will occur. Other clinically relevant indicators of liver disease severity MELD and Child Pugh score, will also be monitored at baseline, study end and 3-monthly during the trial period.

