| **Frequency:** | ALFIE trial nurses may instruct the patient to increase their dose of frusemide (furosemide) or spironolactone no more than every 5 days (following receipt of electrolyte test results). |
| **Procedure for administration:** | Patients/carers will monitor weight daily and those failing to show adequate weight loss over a five day period and with normal kidney function and electrolytes will be directed by the ALFIE trial nurse to increase their dose of diuretics. |
| **Management of Complications:** | Complications of diuretics:  **Renal failure:** refer to treating medical officer  **Hepatic encephalopathy:** refer to treating medical officer  **Electrolyte disturbances:**  **Hypokalaemia:** reduce if K+ <hold frusemide (furosemide) if serum potassium <3 mmol/L and recheck bloods within 72hrs.  **Hyperkalaemia:** reduce Spironolactone if serum potassium >5.6 mmol/L. Hold spironolactone if serum potassium >6.0 mmol/L. Recheck bloods within 72hrs  **Hyponatraemia:** Reduced diuretics if sodium <130mmol/L. Hold diuretics if sodium < 125 mmol/L. Recheck bloods within 72hrs  **Muscle cramps:** Check electrolytes. If severe, may require discontinuation; Discuss with Medical Officer.  Complications are to be managed by the ALFIE trial nurse and/or treating Medical Officer depending on the severity. |
| **Monitoring requirements:** | - Diuretic titrations up in dose should be followed by a blood test in 5 days and electrolyte imbalance managed with consideration of concomitant therapy (conducted by either the ALFIE trial nurse and/or treating Medical Officer). - Diuretic titrations down in response to kidney or electrolyte dysfunction should be monitored closely with blood tests. |
| **Documentation:** | Any dose changes are to be documented in the patient’s outpatient medical record/EPAS and the GP informed. |

| REFERENCES | |
| --- | --- |

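### The Child-Pugh result list on the Appendix N form stops at C12, so totals of 13 to 15 have no box

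*Protocol*

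**What the plan says.** Under Outcomes, in the section Mortality and disease severity, the protocol names as indicators to be followed "Other clinically relevant indicators of liver disease severity MELD and Child Pugh score". Both scores are collected in both arms at baseline and at the end of study, according to the Baseline and End of Study sections and the two activity schedules.

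The collection tool is Appendix N. It has:

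- three laboratory values to write in: "Bilirubin: ______ Albumin: ______ INR";
- three tick options for ascites: "None Slight/controlled on treatment Moderate";
- three tick options for hepatic encephalopathy: "None Grade 1-2 Grade 3-4";
- a tick-box result: "A5 A6 B7 B8 B9 C10 C11 C12".

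The form also gives a link to an online calculator, a field for the blood test date and a comments line. MELD is written in as a number and has no fixed list. No point bands for the laboratory values are printed.

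**The concern.** A result list has to cover every value that its items can produce. This one begins where five items at one point each would put it, but it appears to end three points short of the top. Someone who obtains a total of 13 from the calculator must tick C12, leave the result blank or write the number elsewhere, and the protocol does not say which.

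Scores in that range cannot be ruled out. Participants enter with decompensation, and the eligibility criteria set no upper Child-Pugh limit. The form is also completed when a patient is placed on the transplant waiting list, since the End of Study section makes that an end-of-study visit. At stake is the accuracy of the recorded Child-Pugh total in the most severely ill patients. If the ticked result were analysed as it stands, it would understate severity there and hide deterioration above 12.

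**Working it through.** **Inputs.** From Appendix N: five items; three printed levels each for ascites and encephalopathy; eight result boxes, from 5 to 12. From the inclusion criteria: West Haven grade 0 or 1 at consent. Assumed: each item scores from 1 upward in steps of one, and each laboratory item has *k* bands, with *k* = 3 on the standard scale. The document does not print *k*, so a range is shown.

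**1. Bottom of the list.** 5 items × 1 point = 5. This reproduces A5.

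**2. Top of the list.** Maximum = 3 (ascites) + 3 (encephalopathy) + 3*k* (three laboratory items).

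| Bands per laboratory item (*k*) | Maximum |
|---|---|
| 2 | 6 + 6 = 12 |
| 3 | 6 + 9 = 15 |
| 4 | 6 + 12 = 18 |

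C12 is the top only if every laboratory item has two bands, and nothing in the protocol says so. With three bands the list should run from 5 to 15, which is 11 totals. Eight are printed; 13, 14 and 15 are missing.

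**3. Item combinations without a box (*k* = 3).** There are 3^5 = 243 combinations. A total of 15 arises in 1 way and 14 in 5 ways. A total of 13 arises in 15 ways: one item two points below its maximum (5 ways), or two items one point below (10 ways). Together 1 + 5 + 15 = 21 of 243. These are counts of combinations, not proportions of patients.

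**4. Baseline.** West Haven 0 or 1 limits encephalopathy to the first two options, so at most 2 points. The maximum is 4 × 3 + 2 = 14. Of 3^4 × 2 = 162 combinations, 6 have no box. The Pre-Screening section asks for grade 0 in anyone with an encephalopathy diagnosis. On that stricter rule the maximum is 4 × 3 + 1 = 13, and 1 of 81 combinations has no box. Either way the list is too short at baseline.

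**5. Size if such patients were ticked at C12.** The shortfall is 1, 2 or 3 points for totals of 13, 14 or 15, so the mean understatement is p13 × 1 + p14 × 2 + p15 × 3. The protocol gives no shares, so those below are assumptions.

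| Assumed share at 13 / 14 / 15 | Mean understatement (points) |
|---|---|
| 2% / 1% / 0% | 0.02 + 0.02 + 0 = 0.04 |
| 5% / 2% / 1% | 0.05 + 0.04 + 0.03 = 0.12 |
| 10% / 5% / 2% | 0.10 + 0.10 + 0.06 = 0.26 |

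This applies only if the box is mis-ticked and the tick is then analysed in place of the components.

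**The case against.** The strongest reply is that nothing is lost. All five components are on the same page, so any total up to 15 can be recalculated. Class C starts at 10 and is unaffected, and MELD is entered freely. No instruction tells staff to tick C12 for a higher score. The patients concerned may be few: the encephalopathy rule lowers the baseline maximum, and patients under active palliative management or with expected survival below three months are excluded. Severity is absent from the Study Objectives, and the Statistical methods section allows covariate adjustment without naming Child-Pugh. All of this stands and sets the weight of the point. It does not make the list correct, and the protocol does not say that the score will be rebuilt from the components.

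The printed list might also have been shortened when the text was read from the PDF. Nothing suggests this, since the sequence is unbroken and the MELD part follows, but the original form should be looked at.

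Two stronger readings are tempting. A reader might infer that the severity outcome itself is capped at 12. It is not: only the tick-box is. A reader might also infer that the arms cannot be compared at study end. The protocol uses usual-care bloods ("Collect the information from the most recent bloods taken as part of usual care") without a stated age limit, and only intervention patients have scheduled specialist reviews and nurse-led titration ("Diuretic titrations up in dose should be followed by a blood test in 5 days"). The documents do not support that inference. The form's rule, "most recent – closest to date due", is the same for both arms at study end, and the test date is recorded. Gastroenterologists remain involved in both arms. Nothing shows that control bloods are older or more often taken in acute illness. The titration test is tied to dose changes, not to study end.

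**Conclusion.** The form is wrong as printed, given three bands per laboratory item: totals of 13, 14 and 15 have no box, and at baseline at least 13 is attainable under either encephalopathy rule. The consequence is a possible mis-tick or blank result in the sickest patients of either arm, by one to three points per patient affected. How many are affected is unknown. Because the components are recorded, the error can be repaired in full wherever they are complete. Class C, MELD and the primary endpoint, unplanned liver-related admissions, are untouched. No difference between the arms follows from the short list, since both use the same form. Severity: minor.

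**What to change.** Do one of the following:

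- add C13, C14 and C15 to the result list in Appendix N; or
- state in the protocol that the analysed Child-Pugh score is derived centrally from bilirubin, albumin, INR, ascites and encephalopathy as recorded, and that the ticked result serves only as a check.

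In either case, recalculate the score for forms already completed, starting with those ticked C12 or left blank. The cost is one line on the form or one sentence in the protocol, plus a short recalculation from data already held. No extra blood test or visit is needed. The rule for choosing bloods need not change on this account. If sample age is of interest, the recorded test date allows it to be described by arm.
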